##### For prevention of postpartum hemorrhage

We searched Medline through January 1, 2019, and found 20 RCTs aimed at evaluating the preventive impact on PPH of tranexamic acid administered after delivery in addition to prophylactic uterotonics [19–38]. Only four enrolled women with vaginal deliveries [19–22], the sixteen others including women with cesarean delivery [23–38]. Except for the French Tranexamic Acid for Preventing Postpartum Hemorrhage Following a Vaginal Delivery (TRAAP) trial, which we coordinated and on which this protocol is modeled [22, 39], these RCTs took place in countries with low or middle resources (China, India, Iran, Turkey, Pakistan, and Egypt), had major methodological flaws, and their results could have been affected by their potential for selection, performance, and detection biases. Their findings must therefore be interpreted cautiously, as stressed by several authors [12, 39–45]. The TRAAP trial enrolled 4000 women at standard risk for PPH with a planned vaginal delivery of a singleton live fetus at 35 weeks or more of gestation [22]. The primary outcome — blood loss of at least 500 mL — did not differ significantly between women randomized in the tranexamic acid group and those in the placebo group (RR, 0.83; 95% CI, 0.68 to 1.01; *P* = 0.07).

Sixteen RCTs have thus assessed the effect of tranexamic acid in preventing PPH in women who had elective cesareans; they reported a significantly reduced blood loss in those randomized to receive tranexamic acid, with no effect on the cardinal vital signs or on thrombosis [23–38]. Nevertheless, because of their notable methodologic concerns related to blinding, outcome assessment, and attrition bias, their findings must be considered inconclusive. Furthermore, the external validity of the results observed in middle-income countries appears uncertain, and they lacked adequate power to assess severe adverse events [12, 39–45]. The interpretation of their results thus requires particular caution.

Finally, it is important to emphasize that none of these RCTs included cesarean deliveries during labor [12], when moderate and severe blood loss are both significantly more prevalent than before labor [46].

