Women will be randomized to receive either 1 g of tranexamic acid (Sanofi Aventis, Paris, France; Marketing authorization number: 3400931157618 [1974, RCP rev 06.08.2018]) or placebo (normal saline, Fresenius Kabi, Sèvres, France; Marketing authorization number: 3400941573941, RCP rev 02.01.2018), at a 1:1 ratio. The Clinical Epidemiology Unit (CEU) of the Bordeaux University Hospital will create and securely hold the randomization list for allocations to the tranexamic acid and placebo groups. As in the previous trial [22, 39], a list of treatment units, containing the type of product (tranexamic acid or placebo) and the corresponding treatment number, will be forwarded to the pharmacy department of the Angers University Hospital, a member of the PPRIGO hospital pharmacists’ consortium (Production Pharmaceutique pour la Recherche Institutionnelle du Grand Ouest). The blinded products will be supplied in numbered, labeled boxes, each containing a 10-mL vial of the study drug (1 g of tranexamic acid or placebo according to the randomization list). All boxes and vials will be identically labeled, and the drug packs will be differentiated only by the treatment number. Accordingly, all participants, including caregivers, will be masked and the women’s safety simultaneously guaranteed*.*

The randomization will be centralized and stratified by center and the timing of the cesarean (before or during labor). Randomization numbers will be attributed through a web platform (Ennov Clinical Software). Once a woman has been included and a randomization number assigned to her, she will retain this number even in case of withdrawal from the study.

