### Statistical analysis

As in our previous TRAAP study of vaginal deliveries [22, 39], data analysis and reporting will adhere to the CONSORT guidelines for randomized controlled trials and will be conducted with the trial statistician and researchers blinded to group status. The women’s demographic characteristics and standard risk factors for PPH will be compared between the two groups. The main analysis of the primary and secondary outcomes will be performed in the modified intention-to-treat (ITT) population, defined as women who undergo randomization and have a cesarean delivery (except if they withdraw consent or are deemed ineligible after randomization). We will also analyze two separate per-protocol populations: women from the modified ITT population receiving a uterotonic and then tranexamic acid or placebo in the 3 min after delivery (as prespecified in the protocol) (per-protocol group 1); the other will include women from the modified ITT population receiving a uterotonic and then tranexamic acid or placebo in the 10 min after delivery (per-protocol group 2; for a situation more consistent with routine clinical practice).

The baseline characteristics of the trial participants, the management of the third stage of labor, and protocol adherence will be compared by descriptive statistics. Quantitative variables will be expressed, as appropriate, as means with standard deviations (and compared by Student’s t-test) or as medians with interquartile ranges (compared by the Wilcoxon rank-sum test). Chi-square or Fisher’s exact tests will be used, as appropriate, to compare categorical variables. The effects of tranexamic acid will be expressed as relative risks with 95% confidence intervals for categorical outcomes and as mean differences with 95% confidence intervals for quantitative outcomes. The results will also be expressed as absolute risk differences with 95% confidence intervals for binary outcomes.

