Two prespecified subgroup analyses will examine the primary outcome in subgroups of women at high risk of postpartum hemorrhage. The subgroups will include women who undergo a cesarean during labor and those who are at risk for postpartum hemorrhage according to a composite definition (having at least one risk factor with an odds ratio of 3 or greater in the literature [53]: history of any of postpartum hemorrhage, pregnancy-related hypertensive disorder, multiple pregnancy, or cesarean during labor). Moreover, prespecified subgroup analyses will examine the secondary outcomes in the subgroup of women who undergo a cesarean during labor. We will use the Benjamini–Hochberg procedure to adjust for multiple comparisons of secondary outcomes or subgroups.

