### Sample size

We assumed a 15% incidence of our primary outcome (calculated blood loss > 1000 mL or RBC transfusion before D2) after cesareans in the absence of tranexamic acid, based on the results from a high-quality RCT conducted in the Republic of Ireland with a similar outcome measure (*n* = 2069) [5]. To show a relative reduction of at least 20% in the incidence of postpartum hemorrhage in the tranexamic acid arm — that is, an incidence of 12% or less in this arm, with α = 0.05, 1 − β = 0.80, and a bilateral test, the study will require 2036 women with a cesarean delivery in each group, totaling 4072 participants. A higher number of randomized women must be included given that some will have a scheduled cesarean cancelled, be lost to follow-up, or lack the postpartum blood sample needed to assess the primary outcome (estimated at a maximum of 10%). Accordingly, we plan to include 2262 women in each group, totaling 4524 participants.

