### Timetable

The 28 French participating maternity units perform 92,500 deliveries a year. The average cesarean rate is estimated at 25% in these tertiary university centers (20.4% national rate in 2016 [57]). Considering the trial’s exclusion criteria, and in particular the exclusion of cesareans performed before 34 weeks, we estimate that 18% of parturients, i.e., 16,500/year, will be eligible for the trial in the participating centers. An inclusion period of 24 months should make it possible to recruit 4524 women, if we assume a participation rate of at least 15%. This rate appears realistic given the previous patient recruitment obtained in similar trials in some of the participating centers (TRACOR and TRAAP trials) [22, 51].

The trial is expected to last a total of 27 months, including 24 months of inclusions and 3 months of postpartum follow-up.

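### Randomisation is stratified by center and timing of cesarean, but the only tests named are unadjusted: a small, avoidable loss of precision, with no bias and no shortfall in planned power

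*Protocol article*

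**What the plan says.** - **Allocation** (Protocol article, randomization paragraph after the exclusion criteria): "The randomization will be centralized and stratified by center and the timing of the cesarean (before or during labor").
- **Centers** (Timetable): "The 28 French participating maternity units perform 92,500 deliveries a year". This makes up to 28 × 2 = 56 strata.
- **Tests** (Statistical analysis): Student's t-test or Wilcoxon rank-sum for quantitative variables; for the rest, chi-square or Fisher's "exact tests will be used, as appropriate, to compare categorical variables".
- **Effect measures** (same section): "The effects of tranexamic acid will be expressed as relative risks with 95% confidence intervals for categorical outcomes", plus risk differences and mean differences. No stratified test, regression model or covariate is named. The only adjustment mentioned is Benjamini–Hochberg, for multiplicity.
- **Timing as a prognostic factor**: the Background describes cesareans during labor as the situation "when moderate and severe blood loss are both significantly more prevalent than before labor". The subgroup paragraph lists cesarean during labor in a composite defined by "having at least one risk factor with an odds ratio of 3 or greater in the literature".
- **Baseline values**: a hematocrit and a hemoglobin from the week before the cesarean are inclusion criteria. The hemoglobin outcome is the difference between the predelivery and D2 values; the Objectives also list the change in hematocrit.

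**The concern.** Stratified allocation balances the arms within each center-by-timing cell, so differences in risk between cells no longer contribute to the true variability of the treatment comparison. A plain chi-square or t-test does not know this and leaves that between-stratum variance in its standard error. If the strata predict the outcome, the reported interval is wider than the design warrants and the test rejects less often than 5% under the null. The article's own evidence makes timing prognostic. Center is plausibly so, because the choice of uterotonic, further uterotonics and PPH management all follow local policy.

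The change outcomes raise a second efficiency issue. A raw difference uses the predelivery value with a fixed coefficient of 1, where a regression would estimate the coefficient from the data.

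At stake is precision, not validity. Precision can still matter: the predecessor trial in vaginal deliveries, as the Background reports, ended at RR 0.83, 95% CI 0.68 to 1.01, P = 0.07. Adjustment chosen after a result of that kind is known would be open to challenge; adjustment fixed beforehand would not.

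**Working it through.** **1. The plan's own figure.** Inputs from Sample size: "We assumed a 15% incidence of our primary outcome", 12% under tranexamic acid, two-sided α 0.05, power 0.80. With the pooled variance and no continuity correction:

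n = [1.96·√(2 × 0.135 × 0.865) + 0.842·√(0.15 × 0.85 + 0.12 × 0.88)]² / 0.03² = (0.947 + 0.406)² / 0.0009 ≈ 2036 per group, or 4072 in total, as stated.

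Inflation: 2036/0.9 = 2262.2, against 2262 stated. The sample size therefore rests on the unadjusted test, and its 80% power is correct for that test.

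**2. Primary outcome, timing alone.** Let w be the share of cesareans in labor (assumed 30–50%; the article gives none), p = 0.15 the overall incidence, and p_L and p_P the incidences during and before labor implied by the odds ratio.

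- R² = w(1−w)(p_L − p_P)² / [p(1−p)]
- True type I error of the unadjusted test = 2[1 − Φ(1.96/√(1−R²))]
- Power of the adjusted test = Φ(2.80/√(1−R²) − 1.96)

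Worked case, OR 3 and w = 0.4: p_P = 9.31% and p_L = 23.54% (check: 0.6 × 9.31 + 0.4 × 23.54 = 15.0). R² = 0.24 × 0.1423² / 0.1275 = 0.038, so √(1−R²) = 0.981. The type I error is 2[1 − Φ(1.998)] = 4.6% and the power is Φ(2.855 − 1.96) = 81.5%.

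| Labor OR | R² over w = 0.3–0.5 | True type I error, unadjusted | Power, adjusted | R² × 4072 women |
|---|---|---|---|---|
| 3 | 3.4–3.9% | about 4.6% | 81.3–81.5% | about 140–160 |
| 2 | about 1.5% | about 4.8% | about 80.6% | about 60 |
| 1.5 | about 0.5% | about 4.9% | about 80.2% | about 20 |

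OR 3 is the threshold of the article's composite definition. The article does not say that it applies to this trial's calculated blood loss, so the lower values are shown as well.

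**3. Adding center.** A simulation of 28 equal-sized centers × 2 timing strata, with arms balanced within strata and 4000 replicates per setting, compared the chi-square test with Cochran–Mantel–Haenszel. Center SD was assumed at 0.2 to 0.6 on the logit scale. At OR 3 the stratified standard error was 1.8% to 3.7% smaller and power rose by 0.9 to 2.2 points. Under the null, the unadjusted test rejected at 4.0–4.5% and the stratified test at 4.5–5.5%; the Monte Carlo error at 5% is √(0.05 × 0.95/4000) ≈ 0.3 points. At OR 1.5–2 the standard error was 0.4% to 2.6% smaller.

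**4. Hemoglobin and hematocrit change.** Let s₀ and s₁ be the predelivery and D2 standard deviations and r their correlation within arm.

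- Variance of the raw change: s₀² + s₁² − 2r·s₀·s₁
- Variance after adjusting for the predelivery value: s₁²(1 − r²)
- Difference: (s₀ − r·s₁)², which is never negative

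In large samples, adjustment is therefore at least as precise. With s₀ = s₁ the variance ratio is (1 − r²)/[2(1 − r)] = (1 + r)/2: 0.70 at r = 0.4 and 0.80 at r = 0.6, i.e. 30% and 20% lower. If s₁ = 1.25·s₀, the ratios become 0.84 and 0.94. At r = 0.8 with the same SD ratio, r·s₁ = s₀ and the gain is nil. Neither r nor the SDs are in the article.

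**The case against.** The strongest reply is that the article may not fix a crude analysis at all. The effect-measure sentence names no estimator, and relative risks and risk differences can come from Mantel–Haenszel or a regression. The test list sits in a paragraph that opens with baseline comparisons, and the full protocol or SAP, neither shown, may adjust. This stands in part: one cannot infer that the trial's final analysis will be unadjusted. But the article is not silent. It assigns baseline data, management and adherence to descriptive statistics, then names tests for quantitative and categorical variables generally, leads straight into treatment effects, and offers no other test for outcomes.

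The second reply is that nothing is invalid: the estimate is unbiased, the type I error does not exceed its nominal level, and the power was computed for the unadjusted test. All of this stands. A reader might infer that the trial is underpowered or its primary test unsound, and the documents support neither.

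Two further inferences go too far. One is that change scores lose to adjustment whenever r is below 1, worth 25–43% more women (1/0.80 to 1/0.70). That range needs equal variances and an assumed r of 0.4–0.6, and it concerns secondary outcomes only. The other is a large gain from center, for example with center rates varying by an SD of 7 percentage points around 15%; the article gives nothing on the spread between centers.

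It is also fair that up to 56 strata will include small cells, so the adjusted method has to allow for them.

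**Conclusion.** The point holds as a free improvement, modest for the primary outcome. The design balances on two factors, one of which the article itself calls prognostic, and the named tests use neither. For the primary outcome the cost is a type I error of about 4.6% instead of 5% and roughly 1.3 to 1.5 points of power forgone, given OR 3 for labor and an assumed 30–50% of cesareans in labor. It is less at OR 1.5–2, and somewhat more if centers differ. For hemoglobin and hematocrit change the gain may be larger, at 20–30% lower variance under equal variances and r of 0.4–0.6, but it shrinks if D2 values vary more than predelivery values and can vanish. Labor share, center spread, r and the SD ratio are all assumptions.

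**What to change.** In the Statistical analysis section:

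- State that the main relative risk and risk difference for the primary outcome are adjusted for timing of cesarean and center. Suitable methods are Mantel–Haenszel estimates with the Cochran–Mantel–Haenszel test, or a model with timing as a fixed effect and center as a random effect. Name one, and give a rule for pooling very small centers.
- State that hemoglobin and hematocrit change are analysed by a linear model containing the strata and the predelivery value.
- Keep the crude analysis as a sensitivity analysis.
- If the SAP already adjusts, align the article's wording with it.

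The cost is a few sentences, written before unblinding. The strata are recorded at randomisation and the predelivery values are required at inclusion, so no new data are needed. The sample size need not change.

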### Feasibility

Some participating centers have previously collaborated in two French PPH-related multicenter randomized controlled trials assessing the impact of controlled cord traction (TRACOR trial [51]) and/or of tranexamic acid (1 g) after vaginal delivery (TRAAP trial [22]) on the prevention of PPH. Together they have randomized more than 4000 women with vaginal deliveries for each of these trials and shown their capacity to conduct large trials related to PPH prevention. Moreover, all participating centers belong to a national network called Groupe de Recherche en Obstétrique et Gynécologie (GROG) and have recently participated successfully in several RCTs, demonstrating their ability to run large RCTs assessing perinatal outcomes [54–56].

### Sample size

We assumed a 15% incidence of our primary outcome (calculated blood loss > 1000 mL or RBC transfusion before D2) after cesareans in the absence of tranexamic acid, based on the results from a high-quality RCT conducted in the Republic of Ireland with a similar outcome measure (*n* = 2069) [5]. To show a relative reduction of at least 20% in the incidence of postpartum hemorrhage in the tranexamic acid arm — that is, an incidence of 12% or less in this arm, with α = 0.05, 1 − β = 0.80, and a bilateral test, the study will require 2036 women with a cesarean delivery in each group, totaling 4072 participants. A higher number of randomized women must be included given that some will have a scheduled cesarean cancelled, be lost to follow-up, or lack the postpartum blood sample needed to assess the primary outcome (estimated at a maximum of 10%). Accordingly, we plan to include 2262 women in each group, totaling 4524 participants.

### Timetable

The 28 French participating maternity units perform 92,500 deliveries a year. The average cesarean rate is estimated at 25% in these tertiary university centers (20.4% national rate in 2016 [57]). Considering the trial’s exclusion criteria, and in particular the exclusion of cesareans performed before 34 weeks, we estimate that 18% of parturients, i.e., 16,500/year, will be eligible for the trial in the participating centers. An inclusion period of 24 months should make it possible to recruit 4524 women, if we assume a participation rate of at least 15%. This rate appears realistic given the previous patient recruitment obtained in similar trials in some of the participating centers (TRACOR and TRAAP trials) [22, 51].

The trial is expected to last a total of 27 months, including 24 months of inclusions and 3 months of postpartum follow-up.

### Data management

Each investigator will be responsible for ensuring the accurate recording of the data, which will be completed by clinical research technicians (CRTs) throughout the trial, with Clinsight software. The electronic case report file for each woman will contain 5 components, as previously described [39]:
1 completed by the CRT from the obstetric file: woman’s characteristics, course of the pregnancy, labor, and delivery.1 completed by the CRT about the postpartum events after leaving the delivery room, and the results of the postpartum blood count.1 questionnaire about women’s satisfaction on D2 postpartum, completed by the women, with responses entered secondarily in the electronic file by the CRT.1 questionnaire about the women’s satisfaction and psychological status at 8 weeks postpartum, sent by the CRT to the women and completed by them, with responses entered secondarily in the electronic file by the CRT.1 questionnaire about the occurrence of thromboembolic and any other unexpected events at 12 weeks in postpartum, completed by the CRT during a telephone interview with the woman, with responses secondarily entered in the electronic file by the CRT.

The Methodology and Data management Centre of the Bordeaux University Hospital will handle the data management and statistics centrally, under the supervision of the Scientific Director of the study ([name]).

Quality control will be conducted according to the standard operating procedures of the sponsor, Bordeaux University Hospital. The research in the investigational centers and management of subjects will comply with the Declaration of Helsinki and Good Clinical Practices. CRTs will conduct regular visits to each investigative center and report to the Data and safety monitoring committee (DSMC). During these onsite inspections and in accordance with Good Clinical Practices and as in the previous TRAAP study [39], the following items will be reviewed:
Compliance with the research protocol and the procedures defined thereinPatients’ informed consents, to be verified for all women includedThe source documents to compare with the data reported in the eCRFs for accuracy and consistency of the data and the missing data.End-of-trial visit: archiving of research documents.

### Trial steering committee

A trial steering committee (TSC) will be set up, which will be responsible for overall supervision of the trial. It will meet before the trial starts and then at least every 2 months until the trial is completed. The TSC will meet within a month of every Safety Monitoring Committee meeting to consider their recommendations (as modified from [39]).

### Safety consideration

As in the first TRAAP trial [39], an independent Data and Safety Monitoring Committee will also be formed. Its members will meet yearly to examine recruitment figures, baseline data, and will review the result of the interim safety data analysis when half of the planned sample size has been recruited.

Suspected unexpected serious adverse reactions (SUSARs) will be recorded and reported with the ANSM (National Agency for Drug Safety) approved SUSAR form. As in the first TRAAP trial [39], SUSARs include maternal death, surgery (other than cesarean delivery) in the 12 weeks after randomization, transfusion of more than 4 units of blood, admission to an ICU, deep vein thrombosis, pulmonary embolism, myocardial infarction, seizure, renal failure defined by the need for dialysis, or suspected drug reactions. In case of a SUSAR the form will be filled in by the local coordinator and transmitted to the trial coordinating center at the Bordeaux University Hospital within 72 h. Copies of the form will then be sent to the trial statistician and the chair of the Safety Monitoring Committee*.* The Safety Monitoring Committee may ask for unblinding, while the investigators will remain blinded to the treatment allocation. The ANSM, the trial sponsor, and the Chair of the Ethics Committee will also be informed by the Safety Monitoring Committee if considered appropriate, in particular when SUSARS related to the Investigational Medicinal Products are suspected. Finally, if the Safety Monitoring Committee judges it needed, it can recommend to the Scientific Committee that the trial be stopped.

